### Secondary Outcomes

All other measures (as described in the *Study Procedures* section and in Figure 2) are secondary outcomes. They will be obtained to explore the direction and effect size of any changes as a groundwork for the development of future trials with meaningful end points, if appropriate. HRQoL will be further used in cost-effectiveness analyses. Within GK, cost-effectiveness is being conducted with the Monitoring and Assessment Framework for the European Innovation Partnership on Active and Healthy Ageing (MAFEIP) tool [36] to support evidence-based decision-making processes for all institutions and users in the health care sector. The main objective of the MAFEIP tool is to estimate the outcomes of a large variety of social and technological innovations by providing an early assessment of the likelihood that interventions will achieve their anticipated impact. In addition, MAFEIP also helps identify the drivers of a technology’s effectiveness or efficiency to guide further design, development, or evaluation. To conduct the cost-effectiveness assessment, all costs will be included in a comprehensive impact assessment (eg, hospitalizations, emergency department admissions, and procedures). The costs for treatment as usual will be collected from historical evidence to complement the comparison.

The patterns over 24 hours of accelerometry and heart rate measurements collected *continuously* (epochs defined through user settings ranging from hourly to continuously during workouts) through the smartwatch will be analyzed to retrieve relevant circadian (ie, of approximately 1 day) physiology parameters through cosinor, nonparametric, and hidden Markov model methods [37-40]. The circadian biorhythms parameters that will be retrieved integrate the endogenous body clock [41], physical activity, and sleep cycles [42]. Circadian rest-activity rhythm has shown relevance in oncology with regard to the well-being and overall survival of patients with cancer [43-45].

At 2 and 4 months, participants will also be asked to complete a usability questionnaire to obtain a System Usability Score [46] and a Net Promoter Score [47]. In addition, patients will be invited to attend a participant focus group. The focus group question guide will include two aspects: (1) experience of using the app and smartwatch during the previous 16 weeks and (2) a beta version of a future iteration of the app will be presented to the patients, and potential acceptability of the new features of this beta version will be explored.

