### Study Procedures

Following the provision of written informed consent, the following measures will be obtained and recorded in the case report form (CRFs) at baseline and at the end of the study (16 weeks):

Height (only measured at study entry)Body massBMIWaist circumferenceHip circumferenceMedical historyConcurrent conditionsConcomitant medicationsWHO performance status [15]Cancer type and stageHarms—adverse events.

We will record and report “unexpected” serious adverse events resulting in death, life-threatening complications, hospitalization or prolongation of existing hospitalization, persistent or significant disability or incapacity, congenital abnormality or birth defect, and other “important medical events” that are considered serious if they jeopardize the participant or require an intervention to prevent 1 of the abovementioned consequences.

The following adverse events are considered to be “expected”: anxiety related to the monitoring of symptoms, diet, and exercise; distress related to the regular use of digital well-being technology; cutaneous allergic reactions to the smartwatch; and visual strain with the light-emitting smartphone screen.

The study uses the following questionnaires:

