Participants will then be presented with the mHealth solution: the GK app on a personal smartphone and a smartwatch paired with the SH app. The participant will be trained to use the apps and watch. The GK app features a set of interactive questionnaires to collect the baseline and periodic self-assessment data. Furthermore, the GK app provides timely reminders about the need to complete the self-assessments and data visualization analytics. Finally, the GK app collects and anonymizes data from the smartwatch and SH app for daily data collection on a dedicated remote server. The smartwatch adopted can be configured and used in different ways; each patient will be able to set up complementary apps offering extra functionalities such as the stress level analysis and to identify the preferred patterns of use. Overall, the data generated by the smartwatch will be collected and aggregated on a daily basis, including heart rate, sleep and physical activity patterns, and calories and food intake. The sampling of data will be dependent on the user settings and contingencies, such as charging at night or battery level. Throughout the 16-week study period, the smartwatch will continuously and unobtrusively record habitual physical activity, sleep patterns, energy expenditure, step counts, and oxygen saturation through its biosensors (Figure 1). For example, the amount of moderate and vigorous physical activity completed per week will be obtained automatically through the study using heart rate data recorded by the wearable smartwatch. Specifically, the maximal heart rate will first be predicted using the following formula: maximal heart rate = 207 − (0.7 × age) [33].

**Table 1 table1:** Data collected at each time point of the study.

	Baseline: day 0	Day 1-14	Daily from baseline	Thrice weekly (alternate days)	Weekly	End of the study (4 months +7 or −7 days)
Eligibility	✓					
Informed consent	✓					
Demographics	✓					
Height, weight, BMI, and waist circumference	✓^a^					✓
WHO^b^ performance status	✓					
Medical history or concomitant conditions and medications	✓					✓
Cancer type and stage	✓					
ED-5D-5L	✓^a^					✓
MFI^c^-10	✓^a^					✓
SATED^d^	✓^a^					✓
PACIC^e^	✓^a^					✓
PAM 13^f^	✓^a^					
Issue of smartwatch and Android device if required	✓^a^					
Food diary				✓		
Weight					✓	
Physical activity appointment including cardio-respiratory fitness and muscular strength		✓				
GPAQ^g^		✓				✓
Habitual physical activity assessment		✓				

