Minutes of activity done by patient including strength and balance					✓	
Borg’s CR100 rating of perceived exertion scale					✓	
ESAS^h^			✓			✓
Continuous smartwatch data collection	✓^i^	✓	✓			
Usability questionnaire						✓
Adverse event assessment	✓^i^	✓	✓	✓	✓	✓
Collection of UKONS^j^	✓^i^	✓	✓	✓	✓	✓

^a^Conducted in person at baseline assessment visit.

^b^WHO: World Health Organization.

^c^MFI-10: Multidimensional Fatigue Inventory Short Form.

^d^SATED: Satisfaction, Alertness, Timing, Efficiency and Duration.

^e^PACIC: Patient Assessment of Chronic Illness Care.

^f^PAM-13: Patient Activation Measure–13.

^g^GPAQ: Global Physical Activity Questionnaire.

^h^ESAS: Edmonton Symptom Assessment System.

^i^To be collected from informed consent onward.

^j^UKONS: United Kingdom Oncology Nursing Society.

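### Table 1 does not match the text it should implement: no 2-month usability assessment, no follow-up PAM-13, and performance status and cancer type/stage at baseline only

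*Protocol article*

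**What the plan says.** Three parts of the protocol article fix the assessment times.

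- **Secondary Outcomes** sets two usability assessments: "At 2 and 4 months, participants will also be asked to complete a usability questionnaire". They yield a System Usability Score and a Net Promoter Score. The same section makes all measures other than the primary one secondary outcomes, as described in Study Procedures and in Figure 2 (not shown), and gives their purpose: "They will be obtained to explore the direction and effect size of any changes".
- **Study Procedures** has a list of case report form measures due "at baseline and at the end of the study (16 weeks". WHO performance status and cancer type and stage are on that list. Height is the only item restricted to study entry. PAM-13 appears among the study questionnaires, without time points.
- **Table 1** (in Study Procedures) has six columns: day 0, days 1 to 14, daily, thrice weekly, weekly, and end of study. The row "Usability questionnaire" has one tick, at end of study. PAM-13, "WHO^b^ performance status" and cancer type and stage each have one tick, at baseline. GPAQ is ticked for days 1 to 14 and end of study, while "Issue of smartwatch and Android device if required" is ticked at day 0.

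**The concern.** A schedule table is what research staff normally work from, and an assessment that was not made at its time cannot be recovered later. Where the table has fewer time points than the text, the table is likely to decide what is collected.

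Two of the gaps have a consequence. The Discussion (Study Goals and Expected Findings) names usability as one of three groups of secondary end points. With an end-of-study form only, the scores come from people who stayed, and those who left may have had the most trouble with the app or watch. A 2-month form is the only planned questionnaire that could record the views of people who leave in the second half. For PAM-13, a single baseline value describes the sample but says nothing about change in patient activation.

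The third gap, performance status and cancer type and stage, leaves staff unsure whether to record them again at the end.

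**Working it through.** **Step 1: time points in the text against Table 1.**

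| Measure | Text | Table 1 | Result |
|---|---|---|---|
| Usability | 2 (months 2 and 4) | 1 (end) | direct contradiction |
| Performance status | 2 (baseline, end) | 1 (baseline) | direct contradiction |
| Cancer type and stage | 2 (baseline, end) | 1 (baseline) | direct contradiction |
| PAM-13 | none stated; change needs at least 2 | 1 (baseline) | conflicts with stated purpose |
| GPAQ | none stated | 2 (days 1 to 14, end) | no contradiction |

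For comparison, EQ-5D-5L, MFI-10, SATED and PACIC each have a baseline and an end-of-study tick. The usability, performance status, PAM-13, GPAQ and watch-issue rows all parse to the full six columns, so the missing ticks do not look like damage from text extraction.

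**Step 2: usability.** Inputs: 100 participants (planned maximum) and the amber attrition limit of 40% (Primary Outcome). Assume that a participant who has dropped out does not return the end-of-study form.

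- Table followed: 100 × (1 − 0.40) = 60 contribute a score. Red means more than 40% dropout, so fewer than 60.
- Text followed: let f be the share of dropouts who leave after month 2, and suppose that everyone still in the study at month 2 answers. Then 60 + 40f contribute at least one score. The documents do not give f, so the range is:
  - f = 0: 60
  - f = 0.5: 60 + 20 = 80
  - f = 1: 60 + 40 = 100

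The 2-month form therefore recovers between 0 and 40 participants at the amber limit, depending on when people leave.

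**Step 3: PAM-13.** Change = end value − baseline value. With no end value, the number of computable changes is 0 of 100.

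**Step 4: performance status and stage.** Statistical Considerations plans subgroups by performance status and by whether there is evidence of disease. Baseline values are enough to form them, so no planned analysis is lost.

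**Step 5: GPAQ.** The watch is issued at day 0 and the first GPAQ falls 1 to 14 days later, that is up to 14/112 = 12.5% of the 16 weeks. No GPAQ value precedes the device. The 12.5% is elapsed time and does not measure bias.

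**The case against.** The strongest reply is that only the usability, performance status and cancer type/stage rows contradict the text, and that everything affected is exploratory data from an uncontrolled pilot. On this view it is a table correction. Several parts of the reply stand.

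- **PAM-13.** The text nowhere states an end-of-study PAM-13. The sentence on exploring changes is general, and Figure 2, which helps define the secondary outcomes, is not shown. The point is therefore an inference from purpose. It remains a fair one: a single measurement cannot serve that purpose, and four questionnaires taken at the same baseline visit have both ticks.
- **Usability.** The loss arises only if the table prevails over the text. A 2-month form would still miss earlier dropouts, a focus group also explores experience, and disengagement is captured by the primary outcome. A reader might take 60 of 100 as a floor; it is only the amber limit, and the red category lies below it. That scores from completers would flatter the solution is plausible but not shown.
- **Performance status and stage.** No planned use of the end-of-study values is stated, so the mismatch has little consequence.
- **GPAQ.** A reader might infer that the GPAQ baseline is mistimed and that the device pulls the measured change toward zero. The documents do not support this. They never call the day 1 to 14 GPAQ a baseline, and they schedule it alongside the physical activity appointment. Study Procedures describes goals and coaching based on sleep data and an optional calorie target in the Samsung Health app, and mentions no activity goals. The direction and size of any device effect are unknown.

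The reply does not remove the need to act. Staff cannot follow both schedules.

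**Conclusion.** The point holds, with three parts of unequal weight.

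1. **Usability** is a direct contradiction with a practical cost. Under Table 1, dropouts after month 2 give no score. About 60 of 100 contribute at the amber limit and fewer in red, assuming 100 enrolled and no forms from dropouts.
2. **PAM-13** conflicts with the stated purpose of the secondary outcomes. No change in patient activation can be computed. This rests on reading the Secondary Outcomes section as covering PAM-13, which its wording does.
3. **Performance status and cancer type/stage** are a minor inconsistency.

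The GPAQ timing is not an error. An earlier GPAQ would be a low-cost improvement and no more. The primary engagement outcome and the planned subgroups are unaffected, so the consequences stay within the secondary outcomes. Correction before enrolment is worthwhile because it is cheap and the missing data could not be obtained afterwards.

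**What to change.** - Add a 2-month column to Table 1 and tick usability there as well as at end of study. Have it completed remotely, for example on the online survey platform already used for other questionnaires or in the app. Contact From the Research Team guarantees a call only at week 1, with later calls as needed, so no 2-month contact can be relied on.
- Tick PAM-13 at end of study. If a single baseline measurement is intended, say so and exclude PAM-13 from the measures meant to show change.
- Reconcile the performance status and cancer type/stage rows with the list in Study Procedures: either tick end of study in the table, or mark these items in the text as baseline only, as is done for height.
- Optional: take the first GPAQ on day 0 before the watch is issued, so that a pre-device value exists.

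The cost is a table edit, one short remote questionnaire at 2 months and one further questionnaire at the final assessment. The sample size, the feasibility criteria and the primary analysis do not change.

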**Figure 2 figure2:**
[figure not shown]
Summary of the pilot primary and secondary outcomes, which are categorized as subjective (from questionnaires) and objective (measured or from the smartwatch).

### Exploratory Outcomes

The exploratory end points include the assessment of the precision (sensitivity and specificity) of AI-generated prediction of events based on the longitudinal patient-generated data sets. Specifically, events of interest will be severe symptoms requiring a call to the Acute Oncology Service (ranked amber and red on the United Kingdom Oncology Nursing Society triage tool [48]) or relapse (recurrence or progression) of cancer. Machine learning techniques applied to longitudinal datasets will be used, based on our previous experience [49].

### Data Management

Data in this study are multidimensional and will be collected via a range of sources including paper-based CRFs, paper-based and electronic questionnaires (completed via the GK app), and biometric data obtained from the smartwatches. All anonymized data collected by the NHS research team via paper-based methods will be transferred into a secure digital database, in a locked room, and on a password-protected desktop computer, whose access will be logged and monitored and limited to the research team members involved in the study.

Raw accelerations and heart rate data collected through the smartwatch will be periodically and seamlessly downloaded and sent to the GK app onto the paired smartphone. Afterward, once a day, these data will be automatically and securely uploaded onto the GK repository server through the internet in an anonymized fashion, where they will be kept for further time-series analyses, as previously described.

### Confidentiality and Data Protection Considerations

The sponsor (Betsi Cadwaladr University Health Board) has undertaken a full data protection impact assessment. To protect the confidentiality of participant data, paper-based CRFs and questionnaires will be linked to the participant via a trial identification number and stored in a separate location in the Investigator Site File containing the original consent forms. All paper-based documents will be stored in a locked cabinet in a restricted access office area. Participants will not be required to provide any personal information (such as name and date of birth) to register or use the GK app; instead, they will use the provided study account. The GK app will pull and anonymize data from the SH app, excluding contact details and other information that could be used to reidentify participants. The key linking the participant with the data set will only be held by the NHS research team and never be shared with other organizations.

### Trial Management and Risk Assessment

The sponsor has undertaken a risk assessment in line with the sponsor’s standard operating procedures, and the overall trial has been assessed as moderate risk, principally in relation to the multidimensional monitoring. The trial conduct and progress will be monitored by a trial management group including independent experts and patients to provide advice and support. A trial risk-adapted monitoring plan has been developed to check the research procedures; evaluate overall safety; and assess protocol compliance, data accuracy, and completeness.

### Statistical Considerations

The study’s primary outcome is feasibility, which, by design, is assessed by multiple outcomes (as described above). Arguably, the most important of these is patient engagement with the mHealth solution, and we have defined the solution as feasible if at least 50% (50/100) of the participants engage with the app at least once a week in 8 of the 16 study weeks. If we recruit 100 eligible participants, we will be able to estimate an engagement rate of 50% (n=50) with a 95% CI of +10% or −10%, whereby the width of the CI (in percentage) was calculated as follows:

1.96×√(p×(1−p)/n) **(1)**

where p is the percentage (50%) and n is the intended sample size (100). For this feasibility study, we considered this CI appropriate for estimating drop-off rates in future studies. Finally, we considered this sample size suitable for the preplanned exploratory subgroup analyses.

The main analysis of the primary outcome (compliance) will be performed on an intention-to-treat basis. Similarly, the secondary outcomes will be evaluated on an intention-to-treat basis. However, for the secondary outcomes, preplanned subgroup and sensitivity analyses will also be conducted. They will include (1) subgroups with at least 75% (75/100) of available patient-generated data (from the app and the smartwatch combined) to exclude unengaged participants and focus on the most committed participants, (2) subgroups defined by the performance status and presence or absence of evidence of neoplastic disease, and (3) subgroups defined by sex and median age. For the primary outcome, no form of inference will be performed on the missing data, as they provide the main outcome of the study. For secondary analyses, neither mean imputation nor the last observation carried forward will be used [50]. However, based on the proportion of missing data, exploratory analyses including low-rank approximation–based imputation [51] could be performed to ensure that the observed effect sizes remain of the same order of magnitude with this approach as well.

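### The exploratory age analysis of the secondary outcomes splits participants at the median age; if age acts roughly linearly, this loses about 25% to 46% of the information on age and gives a contrast that is harder to reuse

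*Protocol article*

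**What the plan says.** Statistical Considerations states that "for the secondary outcomes, preplanned subgroup and sensitivity analyses will also be conducted". The third item in the list that follows is "3) subgroups defined by sex and median age". No age in years is given for the cut, so the natural reading is the median of whoever is enrolled. The article describes no analysis with age as a continuous variable.

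The same section says "we considered this sample size suitable for the preplanned exploratory subgroup analyses", with no calculation for the subgroups. The only precision figure concerns the primary outcome: "we will be able to estimate an engagement rate of 50% (n=50) with a 95% CI of +10% or −10".

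Age will be available as a number. Table 1 lists demographics at baseline, and Study Procedures predicts maximal heart rate with a formula that needs age in years: "maximal heart rate = 207 − (0.7 × age". Eligibility Criteria sets a minimum age of 18 and no maximum.

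Secondary Outcomes gives the purpose of these measures: "to explore the direction and effect size of any changes as a groundwork for the development of future trials with meaningful end points".

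**The concern.** A median split treats a participant just above the median like the oldest person in the study, and unlike someone a few months younger who falls just below it. When the outcome changes gradually with age, that discards information the trial already holds. In a pilot of 100 people, where estimates are imprecise anyway, this is an avoidable loss.

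The second issue is reuse. The contrast between the older and younger halves depends on where this sample's median falls and on how widely ages spread around it. A later trial with a different age mix cannot apply the result directly, whereas a slope per year or an estimate at a stated age can be applied.

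What is at stake is limited to how precisely, and in how usable a form, the trial describes whether changes in symptoms, quality of life, sleep or activity vary with age.

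**Working it through.** **The plan's own figure.** The half-width for 50% engagement with n = 100 is 1.96 × √(0.5 × 0.5 / 100) = 0.098, or 9.8 points. This rounds to the stated 10, so the figure is reproduced. No corresponding figure is given for the age subgroups.

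**Inputs.** n = 100 is from Statistical Considerations. Reduced numbers of 80 and 60 correspond to dropout of 20% and 40%, the limits of the green and amber attrition bands under Primary Outcome. The age distribution, the form of the age effect and the strength of the relation are not in the article. They are assumed below and varied.

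**Information kept by the split.** For a linear age effect, the efficiency of the median split relative to continuous age is the squared correlation between age and the above-median indicator.

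- Normal age: in SD units the covariance is 0.3989 and the indicator's SD is 0.5. The correlation is 0.3989 / 0.5 = 0.798, and its square is 0.637 (= 2/π).
- Uniform age on (0, 1): the covariance is 0.125 and the SDs are 0.2887 and 0.5. The correlation is 0.866, and its square is 0.75.
- By simulation: 0.654 for a left-skewed beta(5, 2); 0.646 for a normal with mean 65 and SD 12 truncated to 18–95 years; 0.540 for a heavy-tailed t with 5 degrees of freedom.

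The loss is therefore 36% for normal age, with a range from 25% (uniform) to 46% (heavy-tailed).

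**Effective sample size** (n × efficiency):

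| n analysed | normal age | uniform age |
|---|---|---|
| 100 | 63.7 | 75 |
| 80 | 50.9 | 60 |
| 60 | 38.2 | 45 |

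With heavy-tailed age, n = 100 acts like 54.

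**The same loss as precision.** The interval for the implied age slope widens by 1/√efficiency: 1/√0.637 = 1.25 for normal age, with a range from 1/√0.75 = 1.15 to 1/√0.540 = 1.36.

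**Illustrative power.** The article plans no age test, so this only translates the loss into familiar terms. It uses 20,000 simulated data sets per setting, a two-sided 5% test and an assumed correlation of 0.28.

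| setting | continuous age | median split |
|---|---|---|
| n = 100, normal age | 81% | 62% |
| n = 100, uniform age | 82% | 70% |
| n = 80, normal age | 71% | 52% |

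**Dependence on the sample.** The standard error of a sample median is about 1.2533 × SD / √n for normal age. With n = 100 and an assumed age SD of 10 to 15 years this is 1.3 to 1.9 years, so sampling alone moves the cut. The spread matters too. Under normal age the two halves differ in mean age by 2 × 0.798 × SD, which is 16.0 years for SD 10 and 23.9 years for SD 15. The same effect per year would then give an older-versus-younger contrast half as large again in the second sample.

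**The case against.** The strongest reply is that nothing is being tested. The subgroups are labelled exploratory, the study is a single-arm observational pilot, and no age hypothesis, significance level or correlation is stated. That stands: the power figures are illustrations on an assumed correlation, and the point should be read as one of precision.

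A reader might also take the loss to be a fixed third. The article does not support that. It gives neither the age distribution nor the shape of the effect, and if the effect were a step near the median the split would lose little. The range holds only under rough linearity.

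A reader might infer that the split leaves future trials without usable effect sizes. That is too strong. The stated purpose, to "explore the direction and effect size of any changes as a groundwork for the development of future trials", covers all secondary outcomes, and the whole-sample intention-to-treat evaluation supplies those effect sizes and is untouched. Reporting the observed median in years would also ease reuse, though the contrast would still depend on the age spread.

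Nor does the remark on older adults in Strengths and Limitations strengthen the case. It concerns uptake of technology, not how symptoms, sleep or quality of life change with age.

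Finally, functional form is often left to the analysis plan, and a median split guarantees two groups of similar size where a fixed cut might leave one sparse. The first part does not answer the point, because the article itself names the split. The second is a fair reason not to insist on a fixed cut.

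**Conclusion.** The point holds as a low-severity gain in efficiency and reusability for an exploratory analysis. If age effects on the secondary outcomes are roughly linear, the median split loses about 25% to 46% of the information on age. The loss is 36% if age is normal, when 100 participants act like about 64. The resulting contrast is tied to this sample's age distribution and so is harder, though not impossible, to reuse. The size rests on the assumed linearity and age distribution, neither of which the article gives. The primary outcome, its sample size, the feasibility criteria and the whole-sample secondary analyses are not affected.

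**What to change.** In Statistical Considerations, change the third subgroup item to: *subgroups defined by sex, and age analysed as a continuous variable*. In practice:

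- For ESAS trajectories, enter age in years and an age-by-time term in the mixed-effects models already planned under Study Procedures.
- For measures taken at baseline and week 16, enter age as a covariate in the analysis of change.
- Check linearity simply, for example with a spline with few knots.
- Report estimates with 95% CIs at a few ages within the observed range.
- If a two-group table is kept for display, label it descriptive and give its cut in years.

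This needs one sentence and no extra data, visits or participants. By the article's own account enrolment had not started in January 2024 and analysis follows the database freeze, so on that timeline the change could be made before any data are seen. The small downside is that a functional form must be assumed and checked, and the result is a slope or curve instead of a two-column table.
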